### Inclusion criteria

The inclusion criteria for this study are: pregnant women at less than 16 weeks gestation; singleton pregnancy; body mass index (BMI) of >25.0 kg/m^2^; >18.0 years of age; able to read and understand English and provide informed consent.

### Exclusion criteria

The exclusion criteria for this study are: pregnancy at >16 weeks gestation at recruitment; multiple pregnancy; known pre-existing diabetes, impaired fasting glucose (IFG) or impaired glucose tolerance (IGT); GDM prior to recruitment as diagnosed by early pregnancy glucose testing described below; taking medications likely to influence glucose metabolism (in particular metformin, glucocorticoids and immunosuppressants); medical conditions associated with altered glucose metabolism (in particular Cushing’s syndrome/disease and hepatic cirrhosis); known major fetal abnormality noted on 12 week ultrasound examination; and known ingestion of probiotics via capsules or sachets.

The early pregnancy glucose testing follows a strategy supported by the guidelines of the IADPSG [29]. All women will have their random venous plasma glucose measured. Women with a random venous plasma glucose level of >11.0 mmol/L will be considered as having likely overt diabetes and will undergo appropriate further evaluation with fasting glucose, proceeding to an 75 g OGTT if required. Women with overt diabetes or early GDM will be excluded from this study.

In order to ensure participant safety, we do not want to enrol women with serious early pregnancy disturbances in glucose metabolism. Therefore, to err on the side of caution, we will refer any woman with a random venous plasma glucose between 8.0 and 11.0 mmol/L for a 75 g OGTT. Women who are diagnosed with early GDM on this OGTT will be referred for treatment, and excluded from this study. Conversely, those women with an initial elevated random venous plasma glucose but normal OGTT results will remain eligible for randomization.

### Recruitment facility

This study will be conducted at the Royal Brisbane and Women’s Hospital and the Mater Mothers Hospital in Brisbane, Australia. Both hospitals are major tertiary referral obstetric hospitals. Combined, they care for 10,000 public and 5,000 private births annually.

### Enrollment process

Our recruitment strategy is based on the successful strategy used in a previous pilot study [27]. All women enrolling for pregnancy care at the two centers will be sent a letter inviting them to participate in this study. Those who respond will be screened for inclusion and exclusion criteria during an initial phone call, and if eligible, will be invited to attend a baseline assessment.

### Baseline assessment

At the baseline assessment at <16 weeks gestation after review of the inclusion/exclusion criteria and the initial random venous plasma glucose test, data will be obtained on clinical history and anthropometrics and clinical measurements will be taken (Figure 2).

**Figure 2 F2:**
[figure not shown]
Baseline assessment at 16 weeks gestation including clinical history of the mother as well as anthropometric and clinical measurements.

Dietary intake will be assessed using the Cancer Council Victoria’s Dietary Questionnaire for Epidemiological Studies (Version 2) [30]. The validated food frequency questionnaire (FFQ) [31] comprises a food list of 74 items with 10 frequency response options ranging from ‘Never’ to ‘3 or more times per day’. The FFQ also contains three photographs of scaled portions for four foods (used to calculate a portion size calibrator), questions on the overall frequency of fruit and vegetable consumption, and questions on consumption of foods that do not fit easily into the frequency format (such as breads). The 74 food items are grouped into 4 categories: cereal foods, sweets and snacks; dairy products; meats and fish; fruit, and vegetables. A separate set of questions covers intake of alcoholic beverages. The food composition data used to calculate nutrients are from NUTTAB95, supplemented by other data where necessary. The output includes: kilojoules, detailed macronutrient and micronutrient profiles, as well as glycemic index, and glycemic load. The DQESv2 analysis will be performed by the Cancer Council Victoria following the instructions in the User Information Guide.

Self-reported physical activity will be assessed using the Active Australia Survey (AAS) [32]. The AAS assesses the frequency and duration of participation in walking, moderate, and vigorous physical activity in the past week. Physical activity data will be summed to determine total minutes of weekly physical activity, as per the AAS manual [32]. This captured time spent in activities of walking, vigorous exercise, and vigorous yardwork/gardening. It does not record household chores, occupational or incidental activity [32]. In calculation of minutes of physical activity, minutes of vigorous activity will not be weighted by two as suggested in the AAS manual [32], as we are interested in absolute minutes active, rather than the association between physical activity dose and health benefits that may be dependent on total energy expenditure. This allows the creation of the parametric variable “minutes of physical activity”. This will be capped at 840 minutes, according to the AAS manual [32].

Weight will be measured to the nearest 0.1 kg using a spring balance scale. Height will be measured with a wall mounted stadiometer to the nearest 0.5cm. Waist measurements will be taken with a flexible, inelastic tape measure with measures taken on the skin where the circumference is the smallest with the measure positioned horizontally, parallel to the floor with the patient standing up straight at the end of normal expiration. Hip measurements will be taken at the point where the hip circumference is greatest.

### Intervention

After the baseline assessment, women will be randomly allocated to probiotic or matching placebo trial capsules. Participants will be advised to take their capsule with a cold drink, excluding carbonated and sugared beverages, to maximize survival and potential benefit of the probiotics. All women will be provided with dietary advice that follows current Australian nutrition guidelines for pregnancy [33], including simple advice regarding recommended weight gain in pregnancy [34]. Further dietary advice will be provided as clinically indicated as part of standard clinical care.

### Randomization procedure

Participant randomization will occur based on computer-generated random number codes sealed in opaque envelopes. Participants will be stratified by center and by BMI category (BMI >25-30; BMI >30-40; BMI>40 kg/m^2^).

### Allocation concealment and blinding

Placebo and Probiotic supplements will be identically packaged and refrigerated. All medical staff, research assistants, nursing staff and participants will be masked to the randomized allocation.

### Clinical assessments

#### Comprehensive assessment at 28 weeks gestation

At 28 weeks gestation, all baseline clinical assessments, blood tests, stool samples, questionnaires and an updated medical history will be repeated. At this time point, a 75 g OGTT will be performed to identify women who have developed GDM (primary endpoint of the study).

#### Assessment at 36 weeks gestation

At 36 weeks gestation, weight, waist to hip ratio, blood pressure and medication compliance will be assessed by interview.

#### Post delivery assessment

At delivery, cord blood will be sampled, and umbilical cord and placenta will be collected in a subset of women. Neonatal anthropometry will be collected and fetal body composition will be measured by air displacement plethysmography in a PEAPOD Infant Body Composition System (Cosmed, Rome, Italy) [35] within 3 days after birth.

### Compliance

Compliance with probiotic ingestion will be assessed by: (1) participant interview; (2) monthly telephone follow-up; and (3) change in fecal microbiome at 28 weeks gestation.

### Retention optimization

All women independent of treatment allocation will be seen on at baseline, 28 and 36 weeks gestation, but will also receive a telephone consult monthly or more frequently as required. This is for monitoring of weight, blood pressure, pill count and early detection of adverse events. Women will also be offered further supply of capsules when needed. The additional monthly phone review is also expected to assist with adherence and retention.

### Confirmation of probiotic colonization

Maternal stool carriage of probiotic species will be documented to confirm colonization and quantify the number of *L. rhamnosus* and *B. lactis* species using stool samples. This will be done using a stool sample prior to the first dose of probiotic or placebo and repeated at 28 weeks gestation. DNA will be extracted from the stool sample using previously developed techniques [36,37]. Briefly, microbial DNA extraction involves an enzymatic lysis step followed by bead beating in the presence of high concentrations of sodium dodecyl sulfate salt and EDTA, with final DNA purification by a commercial clean-up kit (Qiagen). Extracted DNA will be tested by quantitative real-time PCR for *Lactobacillus rhamnosus* GG and *Bifidobacterium lactis* BB12 using strain specific primers and probes [38].

### Ethical considerations

The study has been approved by the human research ethics committees of the Royal Brisbane and Women’s Hospital, Mater Health Services and The University of Queensland. Any adverse events will be reported to the clinical trial management committee and the human research ethics committees involved.

### Trial Governance

An independent data monitoring committee, consisting of the Director of Pharmacy at the Royal Brisbane and Women’s Hospital, an ethicist and an independent clinician with clinical trials experience is appointed to assess the progress of the trial after completion of the data for each 100 participants enrolled. Any adverse events that might be due to the probiotics will be reported to the clinical trial management committee and the human research ethics committees of the Royal Brisbane and Women’s Hospital and Mater Health Services.

### Analysis

#### Analysis methods

Data will be analysed using the intention-to- treat principle and no intermediate analyses are scheduled. The primary outcome of the study is diagnosis of GDM at 28 weeks gestation. This will be assessed by a 75 g OGTT. The frequency of GDM will be compared between the groups with binary logistic regression accounting for the initial stratification by site and BMI catrgory. The secondary outcomes will be analyzed with general linear models for continuous outcomes and logistic regression for binary outcomes. All data will be summarized by mean and standard deviation for continuous variables and frequencies for categories.

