### Sample size justification/power calculation

At least one third of pregnant women cared for in Brisbane are overweight and obese, in line with the overweight and obesity rates for the general obstetric population in Australia [26]. In one year, across the Mater Mothers Hospital and the Royal Brisbane and Women’s Hospital, over 3300 overweight and obese pregnant women receive pregnancy care. We anticipate to recruit around 40 women per month across both centers with the recruitment strategy tested in a previous study [27]. Based on the Brisbane cohort within the Hyperglycemia and Adverse Pregnancy Outcome (HAPO) data [28], the rate of GDM amongst women who are overweight and obese is 19.3%. We expect that our screening strategy including a random venous plasma glucose and subsequent OGTT to confirm or exclude the diagnosis of overt diabetes, or early GDM will result in the exclusion of around 5% of women who were included in the HAPO study. This will reduce our expected prevalence of GDM to around 18% (5% of 19.3% is ~ 1%). The previous trial reported a 67% risk reduction [21]. However, even a risk reduction of 50% would be clinically meaningful, and we have based our power calculation on a 50% reduction. To detect a change in the incidence of GDM from 18% to 9%, with a power of 0.8, α of 0.05, and a two-tailed test, the estimated sample size is 226 per group. Allowing for 20% attrition of participants, we will recruit 270 women into each group. We anticipate that it will take 15 months to recruit this sample size.

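### An optional improvement: adding the baseline random plasma glucose to a valid primary model, and reporting risks, could gain a little power at almost no cost

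*Protocol article*

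**What the plan says.** Under Analysis methods, the protocol article states that "The frequency of GDM will be compared between the groups" with "binary logistic regression accounting for the initial stratification by site and BMI catrgory". These are the randomisation factors given under Randomization procedure: "Participants will be stratified by center and by BMI category". No other covariate is listed, and no effect measure (odds ratio, risk ratio or risk difference) is named. The same section says that categorical data will be summarised by frequencies.

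Under Exclusion criteria, "All women will have their random venous plasma glucose measured", and "we will refer any woman with a random venous plasma glucose between 8.0 and 11.0 mmol/L for a 75 g OGTT". Women found to have overt diabetes or early GDM are excluded. Those with a raised random value but a normal OGTT stay eligible. The Baseline assessment section places this glucose test before or at baseline, and the Intervention section places randomisation after it.

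The sample size section plans on the risk scale: "To detect a change in the incidence of GDM from 18% to 9"%, "with a power of 0.8, α of 0.05, and a two-tailed test", giving 226 per group. It adds that "we have based our power calculation on a 50% reduction".

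**The concern.** A covariate that predicts the outcome, is measured before randomisation and is available for everyone can usually sharpen the treatment comparison in a logistic model without threatening validity. Random plasma glucose is a natural candidate. It belongs to the same metabolic pathway as the primary outcome, and the protocol already uses it to pick out women with disturbed glucose metabolism. If it is prognostic, a model with site and BMI category alone forgoes some power.

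Efficiency has some value in this trial. The Discussion concedes that a 30% reduction would be clinically important but would not reach significance.

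The scale of the result is a linked matter. The design is framed in risks, while the coefficient from a logistic model is a conditional log odds ratio. At a control risk of 18% the two scales differ visibly, and adding a prognostic covariate widens the gap. A change to the covariates should therefore come with a stated risk-scale summary.

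**Working it through.** **Inputs from the protocol article.** Risks 18% and 9%; two-sided α 0.05; power 0.80; 226 per group; 270 recruited per group with 20% attrition (Sample size justification); a 30% reduction discussed as clinically important (Anticipated limitations). **Assumed:** the odds ratio for GDM per standard deviation of baseline glucose, from 1.3 to 3.0. The documents give no figure.

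**1. The plan's own figure.** Two proportions, pooled variance under the null, no continuity correction:

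n = [1.960·√(2·0.135·0.865) + 0.842·√(0.18·0.82 + 0.09·0.91)]² / (0.18 − 0.09)²

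= [0.947 + 0.403]² / 0.0081 ≈ 225.1, rounded up to **226**.

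This matches the article. Power at 226 is 80.2% from an unadjusted comparison, so the stated 80% does not depend on any covariate.

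**2. Possible gain from adding glucose.** Simulation with 226 per group, 8,000 trials per scenario, a standard normal covariate, and marginal risks held at 18% and 9%. The treatment effect is tested by a Wald test with and without the covariate. The site and BMI strata were not simulated. The Monte Carlo error of each power is about 0.45 points (√(0.8·0.2/8000)).

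| Assumed OR per SD | AUC | Power without | Power with | Gain (points) | Median adjusted OR for treatment |
|---|---|---|---|---|---|
| 1.0 (useless covariate) | 0.50 | 80.3% | 80.3% | −0.1 | 0.45 |
| 1.3 | 0.57 | 79.6% | 80.2% | 0.6 | 0.44 |
| 1.5 | 0.61 | 80.3% | 81.0% | 0.7 | 0.44 |
| 2.0 | 0.68 | 80.8% | 82.5% | 1.7 | 0.43 |
| 3.0 | 0.76 | 79.8% | 84.8% | 5.0 | 0.40 |

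A repeat run put the bottom of the range at about 0.3 points, so the gain for 1.3 to 2.0 is best described as about 0.3 to 2 points. The first row shows that a useless covariate costs essentially nothing.

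A smaller simulation (3,000 trials per scenario) used 216 per group, which is 270 × 0.80. Power was about 79% without the covariate. With it, power was 80.1%, 82.9% and 83.8% for log odds ratios of 0.5, 0.8 and 1.1 per SD (odds ratios of about 1.6, 2.2 and 3.0).

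**3. Scale of the effect.**

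- 18% to 9%: risk ratio 0.09/0.18 = 0.50; odds ratio (0.09/0.91)/(0.18/0.82) = 0.0989/0.2195 = **0.451**.
- 18% to 12.6% (30% reduction): risk ratio 0.70; odds ratio (0.126/0.874)/(0.18/0.82) = **0.657**.

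The last column of the table shows the further step. With the risk ratio fixed at 0.50, the conditional odds ratio drifts from about 0.45 to as low as 0.40 as the covariate becomes more prognostic.

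**The case against.** The strongest reply is that nothing here is wrong. Logistic regression adjusted for both stratification factors is sound practice. Further covariates and the reported effect measure are commonly left to a statistical analysis plan, which is not shown. That stands, and neither omission is counted as a defect. What remains is a suggested change to a primary model that the article does state.

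Three stronger readings are tempting, and the documents support none of them.

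- *The plan loses power.* It does not lose any against its own target: 226 per group gives 80.2% with no covariate. What it forgoes is a possible extra gain of unknown size.
- *Adjustment repairs the attrition shortfall.* Twenty per cent attrition from 270 leaves 216 per group and 78.3% power by the same formula. That is a separate sample-size matter. Adjustment makes up the difference only if glucose is reasonably prognostic.
- *The plan overstates the effect.* A reader might take an odds ratio of 0.45 as a 55% reduction in risk instead of 50%. But the article never says that an odds ratio will be reported or read as a risk. It speaks of comparing frequencies, and each group's proportions will be available. The validity of the test is unaffected.

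It is also fair to say that the covariate may be weak. It is a random, non-fasting value collected for screening, and excluding women with overt diabetes or early GDM thins the upper range where it would be most informative. Using a test as a referral trigger does not show that it predicts GDM at 28 weeks among the women who remain. This makes the lower rows of gain plausible.

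**Conclusion.** This is a nearly free improvement and not an error. The primary model is valid as written. Prespecified adjustment for baseline random glucose would add about 0.3 to 2 points of power if its odds ratio per SD is 1.3 to 2.0, and up to about 5 points at 3.0. The size rests wholly on that assumed prognostic strength, on a roughly normal covariate with a linear effect on the log odds, and on simulation without the strata. I would expect the lower end, which is a judgement.

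Reporting on the risk scale is the companion step. It matches the planning quantities (risk ratio 0.50 against odds ratio 0.45), and it keeps the result readable once a covariate pushes the conditional odds ratio further from the risk ratio.

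**What to change.** In Analysis methods, state the primary model as logistic regression on treatment, site, BMI category and baseline random venous plasma glucose as a continuous term, with no optional covariates. Specify that the screening random value is used for every woman, including those who went on to a normal OGTT. Keep the test of the treatment term in this model as the single primary test.

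Report the adjusted risk difference and risk ratio with 95% confidence intervals by marginal standardisation: predict each woman's risk under both allocations from the fitted model, average within each allocation, then take the difference and the ratio. The odds ratio can be given as supportive.

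The cost is wording and slightly more programming, plus making sure that the screening glucose is kept in the trial data. The article reports eight women enrolled and no intermediate analyses scheduled, so the change can be made well before unblinding. The sample size need not change on this account.

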## Discussion

### Anticipated limitations

In this randomized control trial, the capacity of two specific probiotic substrains to prevent GDM will be tested. A number of limitations can be envisioned: First, the number of organisms in the probiotic capsules given may be too low to prevent GDM. The dosage of the probiotics is based on the previous study performed in normal weight women [21], however overweight and obese women may require a higher dose. Second, the effect size of the probiotics may be lower than expected. Our power calculations are based on a reduction of the incidence of GDM by 50%. A 30% reduction would not reach statistical significance but would be clinically important. Third, there is a risk that women in both the probiotics and placebo group will perceive a potential advantage from probiotic ingestion and increase the intake of probiotics-containing foods such as yoghurts, even while they are requested not to, thereby blurring the results. The dietary questionnaire obtained at 28 weeks gestation is designed to identify this, should it occur. In all RCTs, there is the risk of non-compliance with the treatment. Regular encouraging mobile phone text messages, phone interviews and review visits will be conducted to improve compliance. At the review visits, capsule counting will be performed to assess compliance. Additionally, comparison of the stool samples provided at baseline and at 28 weeks gestation for the species provided by the probiotics will give an objective biological measure of compliance [39].

### Clinical significance of the study

This trial will evaluate the efficacy of probiotic ingestion from early pregnancy to prevent GDM in a high-risk group of women who are overweight and obese. If successful, probiotics would offer a therapeutic option for the prevention of GDM that is simple, cheap and easy to incorporate into standard clinical care.

### Trial status

This RCT started enrolling in November 2012. Currently eight participants have been enrolled.
